#### Blinding

The results dataset will be stored with the study arm identity blinded by way of a unique code for each study participant. The key to this code will be held (independent of the dataset for analysis) by the independent statistician, the chair of the data monitoring committee (DMC) and the principal investigator (PI). The PI needs to know practice group allocation to conduct the intervention group training workshops. The PI will not be involved in data collection, entry, modification or analysis.

Individual patients will remain blind to the presence of two study arms throughout the course of the trial. Consultation appearance will be similar from a patient perspective, except that intervention arm participants may be provided a FREE booklet and referred to the FREE website. Control arm participants may be given other informational materials (e.g., ACC pamphlet) or be referred to other information sites (e.g., patient.org). Even if a patient perceives he/she is receiving a different approach from previous GP LBP consultations, they will remain blind to the study hypothesis.

All patient participant data submitted on paper surveys will be entered or checked by a research assistant blind to group allocation. Data entered by participants through electronic surveys will be checked for completeness and anomalous responses.

Data cleaning and analysis will be conducted by the trial statistician who is blind to group allocation. Once analysis is complete, the results will be unblinded. To eliminate the risk that the trial statistician may have been inadvertently exposed to practice codes during the conduct of the trial, these will be replaced with new codes in the dataset prior to the trial statistician’s receiving the data. Only the independent statistician and the chair of the DMC will have access to the key for these new codes.

GPs and practices will necessarily be unblinded following group allocation because the need for training means GPs will know whether they are in the intervention or control arm prior to patient recruitment. GPs will be aware of their study allocation when completing baseline measures. This is necessary in order to minimise the time between completing baseline measures and receiving FREE training or starting patient recruitment. The content of the intervention will be unknown to all GPs at the time they complete their baseline questionnaire.

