**Fig. 4 Fig4:**
[figure not shown]
Standard Protocol Items: Recommendations for Interventional Trials (SPIRIT) figure for general practitioner participants. *General practitioners were enrolled between 4 weeks and 1 day pre-randomisation. ^†^Allocation occurred between 5 weeks and 33 weeks before training was received. ^‡^Time point when intervention group practices attended initial training workshops. ^§^Assessment completed by intervention group participants only. *FREE* Fear Reduction Exercised Early, *HC-PAIRS* Health Care Providers’ Pain and Impairment Relationship Scale, *Back-PAQ* Back Pain Attitudes Questionnaire

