### Statistical analysis

Statistical significance will be judged with an α of 0.05. All results will be reported as estimates of effect size (e.g., mean difference, risk ratio, number needed to treat [NNT]) with 95% CI. All analyses will be conducted on an intention-to-treat basis.

Analyses will also account for clustering of data as appropriate. For the patient-level outcomes, this clustering will be specified at the GP level using random effects specifying the GP. Whereas randomisation is at the practice level, clustering effects on outcome values are expected to be driven mostly by inter-practitioner variability. For the GP-level outcomes, clustering will be specified at the practice level. The stratified randomisation will be handled by including the practice size stratum identifier in analytical models (less than or equal to eight FTE GPs, more than eight FTE GPs).

In most instances, analysis will be conducted using linear mixed models (for continuous numerical outcomes such as the RMDQ) or generalised linear mixed models (for categorical outcomes such as satisfaction levels). These models allow for inclusion of data from between baseline and the final endpoint to better estimate the differences at the main endpoint in the presence of missing follow-up data [60]. These models will be adjusted for important baseline covariates (age, sex, socioeconomic status, current back pain duration and nature [constant or episodic], receipt of recent or ongoing non-GP health care for back pain, previous history of back pain, baseline disability and baseline psychological factors [pain self-efficacy and recovery expectations]) [61]. The analysis will also be adjusted for baseline Health Care Providers’ Pain and Impairment Relationship Scale (HC-PAIRS) scores as measured at the level of the GP (as a measure of baseline treatment competence). We will analyse categorical outcomes using generalised linear mixed models (conditional treatment estimates) and generalised estimating equations (marginal treatment estimates) for each outcome: The former approach is to be considered the primary analysis for that output because the conditional treatment effect estimates relate to expected gains for each patient [60, 62].

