### Limitations

FREE was initially planned to be delivered during the first consultation which someone receives for an episode of acute LBP, and this study was designed to explore the effect of FREE in this population. The study population was expanded to include people with LBP of any duration for two reasons. Firstly, presentation rates of eligible patients to the first recruitment sites was unacceptably low and indicated that recruitment targets would not be met within time frames that were acceptable to either participating practices or the project budget. Secondly, feedback from participating GPs indicated that these restrictive recruitment criteria excluded most of the patients with LBP they commonly saw. Consequently, the generalisability of study findings was likely to be limited. The revised recruitment criteria are similar to those used in previous LBP primary care research [67]. A sensitivity analysis of the main outcomes will be performed restricted to the original study population of participants with acute LBP.

GPs will complete baseline measures post-randomisation (but prior to receiving training). Training requires that all participating GPs in a practice attend a 4-h training session together. Although it would be preferable to have all GPs complete baseline measures prior to randomisation, this is not possible, given the lead-in time required to schedule and co-ordinate training sessions with the practices. GPs will be aware of whether they will receive training, but they will not be aware of the content of the intervention when they complete baseline measures. It is possible that knowledge of group allocation could affect GPs’ responses when completing baseline measures; however, it is considered more important that these be completed close to when training is received and patients are recruited. GP measures are not the trial’s main outcome, and patients are recruited while blind to group allocation.

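### The RMDQ model adjusts for a GP belief score collected after randomisation from GPs who know their arm, which may bias the primary estimate for little gain in precision

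*Protocol article*

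**What the plan says.** The Statistical analysis section plans "linear mixed models (for continuous numerical outcomes such as the RMDQ" and generalised linear mixed models for categorical outcomes. After listing the patient covariates, it adds adjustment for baseline "HC-PAIRS) scores as measured at the level of the GP (as a measure of baseline treatment competence".

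On when and how that score is obtained:

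- Limitations: "GPs will complete baseline measures post-randomisation (but prior to receiving training".
- Blinding: "GPs will be aware of their study allocation when completing baseline measures".
- Fig. 4 legend: "Allocation occurred between 5 weeks and 33 weeks before training was received". The Blinding section ties the questionnaire to training or to the start of patient recruitment, so it can fall well after allocation.
- Blinding, as a safeguard: "The content of the intervention will be unknown to all GPs at the time they complete their baseline questionnaire".
- Limitations, as a concession: "It is possible that knowledge of group allocation could affect GPs’ responses when completing baseline measures".

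The Limitations section accepts this for three reasons: the measures should be taken close to training and recruitment, GP measures are not the main outcome, and patients are blind when recruited. The article describes no patient-outcome analysis without HC-PAIRS.

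**The concern.** A covariate protects a randomised comparison only if allocation cannot affect it. The patient covariates meet that condition: patients complete them before the consultation, unaware that two approaches are being compared. GP HC-PAIRS is the only listed covariate supplied by people who know their arm.

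If knowing the arm moves the answers, the adjusted treatment effect moves by the slope of RMDQ on the score times the arm difference in reporting. The protocol saw the reporting risk but weighed it only for GP measures as outcomes. Neither the point about the main outcome nor the point about blinded patients covers the score's use inside the primary model.

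At stake is the RMDQ mean difference, and with it the non-inferiority criterion, which uses the same difference and its confidence interval.

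**Working it through.** **Inputs from the Sample size section.** Difference 2.5, SD 6.0, power 80%, alpha 0.05 (taken as two-sided), GP ICC 0.05, 5 completers per GP, 22 GPs per arm, 20% loss.

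**The plan's own figures.**
- Individually randomised: 2 × (1.96 + 0.842)² × 36 / 6.25 = 90.4, so 91 per group.
- Design effect: 1 + 4 × 0.05 = 1.20. 91 × 1.20 = 109.2, so 110 per group.
- 110 / 5 = 22 GPs per arm. 220 / 0.8 = 275 patients.

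All of these reproduce.

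**Assumptions.** The article gives neither of the two quantities that decide the size:
- *r*, the correlation of HC-PAIRS with the GP effect on RMDQ: taken as 0.3 to 0.5, so the score explains r² = 9 to 25% of GP variance.
- *d*, the arm-related shift in answers in SD units: taken as 0.2 to 0.5.

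**What the score can explain.** GP variance = 0.05 × 36 = 1.8, so the GP SD is 1.34 points. Patient variance within GP = 0.95 × 36 = 34.2, or 34.2 / 5 = 6.84 per GP mean.

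**Gain from keeping it.** Variance of the difference = 2 × (1.8 × (1 − r²) + 6.84) / 22, before any cost of estimating the slope.

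| r | GP variance explained | SE | SE reduction | Power |
|---|---|---|---|---|
| 0 (score dropped) | 0% | 0.886 | – | 80.5% |
| 0.3 | 9% | 0.878 | 0.9% | 81.3% |
| 0.5 | 25% | 0.863 | 2.6% | 82.6% |
| 1.0 (ceiling) | 100% | 0.789 | 11.0% | 88.7% |

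**Possible bias.** Size = r × 1.34 × d.

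| r | d = 0.2 | d = 0.5 |
|---|---|---|
| 0.3 | 0.08 (3% of 2.5) | 0.20 (8%) |
| 0.5 | 0.13 (5%) | 0.34 (13%) |

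Against the SE of 0.886, the range is 0.08 / 0.886 = 0.09 to 0.34 / 0.886 = 0.38 standard errors. At r = 0.3 and d = 0.5, an ICC of 0.01 to 0.10 gives 0.09 to 0.29 points.

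**Simulation check.** Regression of GP means on arm and score, 22 GPs per arm, 20,000 runs, true effect −2.5:

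| r | d | Mean, adjusted | Mean, unadjusted | SE, adjusted | SE, unadjusted |
|---|---|---|---|---|---|
| 0.3 | 0 | −2.50 | −2.50 | 0.890 | 0.888 |
| 0.3 | 0.5 | −2.70 | −2.49 | 0.918 | 0.889 |
| 0.5 | 0.5 | −2.84 | −2.51 | 0.898 | 0.884 |

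The bias matches the formula; its direction here is set by construction. With 44 GPs, the small theoretical gain at r = 0.3 disappears once the slope has to be estimated. Patient-covariate adjustment and between-practice variance were not modelled.

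**The case against.** The strongest reply is that after randomisation is not after treatment. GPs answer before training and do not know what it will teach, so the only route to bias is that knowing one will or will not be trained moves answers on a pain-belief scale. The article says this is possible and gives no evidence that it happens. This stands, and it is why the bias must be called possible and modest.

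Second, with up to ten practices randomised and only practice size stratified, GP beliefs may differ between arms by chance, and adjustment could correct that. On the formulas above, squared bias (r² × 1.8 × d²) equals the variance saved (r² × 1.8 × 2/22) at d = √(2/22) = 0.30 whatever r is. Below that shift, adjustment does not raise mean squared error in theory; estimating the slope pulls the break-even somewhat lower. This stands in part. But chance imbalance is already reflected in the confidence interval, a reporting shift is not, and this score cannot tell the two apart.

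Three stronger readings are not supported:

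- A reader might infer that the primary estimate is biased. Neither the shift nor the association is documented.
- A reader might infer that a GP without a questionnaire would leave the primary model with all of that GP's patients, undermining intention to treat. That presumes complete-case handling. The article does not say how missing covariates are treated, and this is commonly left to the analysis plan.
- A reader might extend the point to the GP outcomes. The GP outcomes section states baseline adjustment only for the two vignette analyses; for continuous GP outcomes, HC-PAIRS included, it names only linear mixed models.

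**Conclusion.** The point holds in a limited form. The protocol specifies a covariate in its primary model that, by its own account, could be affected by knowledge of allocation, and its reasons for tolerating this do not address that use.

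Under the assumed ranges, the possible bias is about 0.08 to 0.34 RMDQ points (3 to 13% of the 2.5-point target), of unknown sign. The return for keeping the score is about 1 to 3% in standard error on the same assumption. The 11% ceiling would need the score to explain all between-GP variation. These sizes rest on the protocol's ICC and SD and on assumed values of *r* and *d*; only the timing and the lack of blinding are documented. The change is worth making because it is cheap and removes the question, not because serious bias has been shown.

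**What to change.** While the trial statistician is still blind, amend the Statistical analysis section so that the primary patient-outcome models omit GP HC-PAIRS. Keep the practice-size stratum and the patient covariates collected before the consultation. Report the HC-PAIRS-adjusted models as a sensitivity analysis, and add to the Limitations section that the score's timing also bears on those models.

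The sample size is unchanged; power without the score is 80.5% on the protocol's assumptions. The costs are:

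- a documented amendment to a prespecified model after patient recruitment has closed (31 July 2017);
- about 1 to 3% in standard error under the stated assumption, more if the score explained more of the GP variance;
- loss, in the primary model only, of the ability to correct chance imbalance in GP beliefs.

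A pre-randomisation score can no longer be collected, so the choice of model is the remedy that is left.

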#### Non-inferiority criterion

If the lower bound of the 95% CI for the RMDQ mean difference sits above −2.5 points (the minimal clinically important difference), then we will take this as evidence that the intervention is no worse than current management.

### Patient cost-utility analysis

By performing a cost-utility analysis, we will estimate the mean incremental cost per quality-adjusted life-year (QALY) gained (with QALYs to be calculated with the NZ EQ-5D Tariff 2, as recommended by the New Zealand Pharmaceutical Management Agency [64, 65]) from health care system, ACC and societal perspectives. Reference costs will be assigned for (1) all health care items to allow direct comparison and decrease patient recall requirements, (2) paid work (based on the mean income for someone of the participant's age and gender) to avoid data being skewed by participants with high income and to make results more generalisable to the general population, and (3) unpaid/voluntary work (based upon the minimum wage). The human capital approach will be used for work loss. Because each patient will be followed for 6 months, discounting will not be necessary.

We will report the incremental cost-effectiveness ratio and the monetary incremental net benefit with 95% CI around the estimates. Bootstrapped data will be displayed on a cost-effectiveness plane, and cost-effectiveness acceptability curves will be calculated to determine the likelihood that FREE will be considered cost-effective using one, two and three times gross domestic product per capita as policy-relevant willingness-to-pay thresholds. We will report results from sensitivity analyses by varying inputs over a range of feasible estimates for costs or effects of important variables that are likely to have wide variability (e.g., between small towns and large cities, or chance variability introduced by large costs in a single individual in one group).

### Patient process measures

The aim of mediation analysis will be to examine the *pathways* through which the intervention influences outcomes. We will examine how changes in patient beliefs and attitudes (process variables in Additional file 4) from baseline to week 2 mediate the impact of FREE on the primary outcome (RMDQ score). These analyses are being planned using structural equation modelling or structural mean models approaches [66].

### GP outcomes

As per the patient outcomes, all analyses for GP outcomes will be conducted on an intention-to-treat basis. Clustering of responses will be handled by including a random effect for GP practice in analytical models*.* Continuous outcomes (e.g., HC-PAIRS, confidence scores) will be analysed using linear mixed models. Reported clinical behaviour relating to the case vignette (categorical outcome from five options) will be compared in two ways [56]:Changes in response proportions across the entire range of responses will be compared between arms using a generalised linear mixed model with a cumulative logit link function (to allow for ordinal nature of outcome), adjusted for baseline values and including a random effect for GP practice (to handle clustering).Changes in the proportions of consultations following ‘guideline-consistent’ reported behaviour (in contrast to ‘guideline-inconsistent’ behaviour) will be compared between arms using a generalised linear mixed model with a logit link (i.e., akin to a logistic regression specification), with responses categorised into two levels (‘guideline-consistent’ versus ‘guideline-inconsistent’ [56]). This analysis will be adjusted for baseline values and include a random effect for GP practice to handle clustering.

GP behaviour in the initial LBP patient consultation will be compared between intervention and control group GPs using data from patient management systems and patient report (separate analyses for recommendations regarding work, activity and medication, as well as for referrals to physiotherapy/osteopathy/chiropractic, specialist, x-rays or other scans). Summary statistics will be calculated for each GP (e.g., proportion of patients seen by that GP who reported being advised to take time off from work) and compared between study arms using a linear mixed model for the mean percentage of patients meeting each indicator.

### GP process measures

Process evaluation will be undertaken using mixed methods. Both quantitative and qualitative data from a range of participants and from various sources will be analysed. These include the sample of audio-recorded consultations which will be assessed for fidelity to the FREE approach using a checklist based on FREE, EMR data and the patient-reported consultation content, and GP questionnaires. In order for an audio-recorded consultation to be judged as being faithful to the FREE approach, it must include (1) exploration of patient concerns (item 1 from the Audio Recording Checklist), (2) explanation and reassurance (items 4c–4f or item 7) and (3) work and/or activity advice (item 5). The mean duration of FREE approach consultations will be compared with control consultations using linear mixed models (allowing for clustering by GP; no adjustment for any baseline values).

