### Randomisation, allocation concealment and blinding

#### Randomisation

General practices will be randomly assigned to either the intervention or control group (i.e., all GPs in a practice will be randomised to the same arm) with a 1:1 allocation, using a computer-generated randomisation schedule stratified by the number of FTE GPs within the practice (≤8 versus > 8 FTE). The aim of the stratification procedure is to ensure that approximately equal numbers of GPs are allocated to the intervention and control groups. An independent statistician will conduct the randomisation process. Analysis of outcomes will include this practice size stratification variable as a fixed effect to account for the impact of this design element on study results.

GP participants will be randomised by practice for the following two reasons: (1) Individual patient randomisation is not feasible, because GPs may find it difficult to provide ‘usual care’ after learning about the new approach, which would result in contamination of results from control patients; and (2) randomisation at the level of the individual GP (rather than practice) may result in contamination effects if intervention GPs discuss the FREE approach with control arm GPs within their practice.

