#### GP process measures

To examine the mechanisms by which FREE might impact GP behaviour, we will collect measures related to GP learning [57], satisfaction with training, treatment fidelity and proposed mechanisms of impact (Additional file 5) [58]. Intervention group GPs will record the number of FREE consultations they conduct during the experiential learning period. Associations between consultation count and GP knowledge, beliefs, behaviour, confidence and patient outcome will be analysed to explore whether a minimum number of training consultations is required to become competent in the approach.

Consultation recordings will be analysed to explore whether FREE consultations are longer than usual care LBP consultations. One consultation recording will be randomly selected from each GP with audio recordings available for content and thematic analysis. All consultations selected will be analysed using the Consult Audio Recording Checklist. The researcher conducting this analysis will be blind to group allocation.

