## Discussion

A number of tools exist to classify patients presenting with LBP and allocate treatment on the basis of risk of poor outcome [68, 69]. These have been found to have acceptable predictive ability for disability outcomes but poor predictive ability for persistent pain [70]. Encouraging GPs to simply apply these screening tools and plan subsequent referred care on the basis of risk profiles misses the opportunity for a positive therapeutic encounter delivered by the GP at the point on entry into the health system. Even if a GP is to base treatment decisions on a classification process, there is still a need to ensure this first interaction with a health practitioner is delivered in an optimal manner and aids rather than impedes future care. Because FREE is delivered by a GP within normal consultation time, it does not add cost to an episode of care. Therefore, if FREE is found to be effective and does not increase other costs, it may be a cost-effective method of improving LBP care.

In a previous study in which Dutch GPs were trained to explore and address psychosocial factors in patients who had subacute LBP, researchers did not find any clinically relevant benefits [71]. Jellema et al. [72] concluded that this was because GPs were only moderately successful at identifying psychosocial factors and postulated that 20-minute consultations were insufficient for restructuring patients’ dysfunctional beliefs. The FREE approach differs from the intervention of Jellema et al. in three key ways. Firstly, it aims to restructure the basic GP consultation rather than providing it by way of an additional appointment. This makes the approach appear to be standard practice rather than an add-on, allows the earliest possible intervention, minimises the risk of the GP unwittingly increasing patient threat or fear through their usual practice [73], and ensures that a consistent approach can be used in any subsequent encounters. Secondly, FREE bases the exploration of psychosocial factors around the identification and minimisation of factors which increase patient threat in relation to their back pain rather than including all potential psychosocial influences which may overwhelm GPs [33]. Thirdly, it also provides the patient with a booklet and website which support and reinforce the information provided by the GP.

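### The consultation-duration model, read literally, drops the practice-size stratum and makes no use of episode type; this costs precision rather than causing bias

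*Protocol article*

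**What the plan says.** Under Measures, GP process measures, the purpose is exploratory: "Consultation recordings will be analysed to explore whether FREE consultations are longer than usual care LBP consultations". The later GP process measures section gives the method: "The mean duration of FREE approach consultations will be compared with control consultations using linear mixed models". A bracket then completes the specification: "allowing for clustering by GP; no adjustment for any baseline values".

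Two general statements concern the stratification factor, practices with up to eight versus more than eight full-time-equivalent GPs. The Randomisation section says "Analysis of outcomes will include this practice size stratification variable as a fixed effect". The Statistical analysis section says "The stratified randomisation will be handled by including the practice size stratum identifier in analytical models" and states no exception.

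For patient outcomes, the Statistical analysis section adds "These models will be adjusted for important baseline covariates". The list that follows includes duration and nature of the current back pain and recent non-GP care. The Aim section defines a new acute episode as pain of under 6 weeks with no back-pain care in the previous 3 months. The same Statistical analysis section puts every analysis on an intention-to-treat footing.

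**The concern.** The duration model is the one place where the article fixes a model and rules out adjustment in so many words. Practice size is a randomisation stratum. If consultation length differs between small and large practices, leaving the stratum out moves that difference into the between-GP variance and inflates the standard error of the arm comparison. The test then detects a real lengthening less often than it should.

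The direction matters because the convenient answer here is that FREE takes no longer. The Discussion argues from it: "Because FREE is delivered by a GP within normal consultation time". The recordings provide the only comparison of consultation length that the article describes.

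Episode type is a second, smaller matter. Patients with pain of any duration are now eligible, so recordings will mix new episodes with ongoing problems, and these may differ in length. With at most ten practices, and patients recruited after randomisation, the mix could differ between arms by chance. The plan has nothing in this model to correct for that.

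**Working it through.** **The plan's own figures.** The article states none for duration. Its only calculation, for the primary outcome, reproduces: 2 × (1.96 + 0.8416)² × 6.0² / 2.5² = 90.4, so 91 per group; 91 × [1 + (5 − 1) × 0.05] = 109.2, so 22 GPs × 5 = 110 per group; 220 / 0.80 = 275. None of this depends on the duration model.

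**The passages side by side.** The Statistical analysis rule covers analytical models in general. The Randomisation rule covers analysis of outcomes. The duration bracket names GP clustering and excludes baseline values without mentioning the stratum. The text does not settle whether the stratum term stays.

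**Effect of leaving out the stratum (illustration).** All values here are assumed except the limit of ten practices, the 1:1 stratified allocation and five patients per GP (taken from Sample size):
- 6 small practices with 3 recruiting GPs each and 4 large practices with 6 each, giving 18 + 24 = 42 GPs, 21 per arm
- 5 recorded consultations per GP
- SD of 5 minutes within GP and 2 minutes between GPs, with no further practice-level variance

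Step 1. Variance of a GP mean: 2² + 5²/5 = 9. True SE of the arm difference: √(9 × 2/21) = 0.926 minute.

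Step 2. Each arm has 9 GPs in small practices and 12 in large ones, so the point estimate is the same with or without the stratum. Only its estimated SE changes.

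Step 3. A stratum effect of s minutes adds s² × (18/42) × (24/42) = 0.245 s² to the apparent between-GP variance if the term is omitted. The SE is then inflated by √(1 + 0.245 s²/9), and the type I error is P(|Z| > 1.96 × inflation).

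| Stratum effect | SE inflation | Type I error without stratum, by formula | Simulated, without stratum | Simulated, with stratum |
|---|---|---|---|---|
| 0 min | 1.00 | 0.050 | 0.050 | 0.049 |
| 2 min | √(9.98/9) = 1.053 | 0.039 | 0.039 | 0.051 |
| 4 min | √(12.92/9) = 1.198 | 0.019 | 0.020 | 0.052 |

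The simulation (4,000 null trials per row, analysed on GP means) agrees with the formula. Its mean estimates lay between −0.03 and +0.01 minute, so there is no bias.

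**Case mix.** With an assumed 3-minute effect of episode type and between-practice variation in the mix (SD 0.10), the null estimate again centred on zero. Type I error was 0.044 without the stratum and 0.046 with it. Both are within two simulation standard errors of 0.05 (one is √(0.05 × 0.95/4000) = 0.0034).

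A realised imbalance does shift one trial's estimate, by difference in share × difference in minutes: 0.05 × 1 = 0.05 minute at the low end and 0.20 × 5 = 1.0 minute at the high end. The upper value is about one SE (1.0/0.926 = 1.08).

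**The case against.** **Is this a contradiction?** A reader might say the protocol breaks its own stratum rule. The documents do not establish that. In the GP outcomes section, adjusting for baseline values goes with vignette responses: "This analysis will be adjusted for baseline values and include a random effect for GP practice to handle clustering". There the phrase appears to mean an earlier measurement of the same response. No baseline consultation duration is described, so the bracket may only record that none exists. The Randomisation rule is limited to outcomes, and duration is a process measure. This objection stands as far as it goes. Against it, the Statistical analysis rule has no such limit, and the word any in the bracket invites the wider reading.

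**Is the comparison biased?** A reader might infer that wider eligibility makes the unadjusted result misleading. It adds variety to both arms and does not itself create a difference between them. Similar-sized intervention and control practices recruit simultaneously, all eligible patients are invited, and scripts are identical. A prespecified unadjusted comparison is legitimate, and no stated rule requires covariate adjustment of a process measure. What remains is chance imbalance, of which the documents give no sign.

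**Are only faithful consultations compared?** The model sentence comes shortly after the fidelity definition, so a reader might infer selection of consultations that meet it. The text points the other way. The checklist is applied to one randomly selected recording per GP, whereas a model with clustering by GP implies several, most of which would carry no fidelity rating. The intention-to-treat rule also covers this analysis.

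**Does the cost-effectiveness case depend on it?** Not solely. The Discussion's statement is conditional on effectiveness and on other costs not rising, and costs have their own analysis.

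**Conclusion.** The point holds as a minor one. Read literally, the duration model omits a stratification factor that the general rule includes, and it forgoes a relevant covariate already collected. The expected cost is precision: an interval about 5% to 20% too wide, and a type I error of about 0.04 to 0.02 instead of 0.05, if practice size shifts duration by 2 to 4 minutes. With no stratum effect the cost is nil. Chance case-mix imbalance could move a single estimate by 0.05 to 1.0 minute.

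These sizes rest entirely on assumed variances, practice mix, visit lengths and imbalances. The conservative direction also assumes no practice-level variance beyond the stratum. Such variance, in a model that clusters only by GP, would push the type I error the other way. The primary analysis and the sample size are not touched.

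**What to change.** In the later GP process measures section, replace the exclusion of baseline values with a statement that:

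1. the duration model includes the practice-size stratum as a fixed effect, as in Statistical analysis;
2. it adjusts for new acute episode, as defined under Aim, versus other, either as a covariate or in a named sensitivity analysis;
3. all recorded consultations are compared by randomised arm, whether or not they meet the fidelity definition, in line with the intention-to-treat rule.

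The third item only confirms the more natural reading. If the exclusion was meant solely to say that no earlier duration measurement exists, say that instead and confirm that the stratum term stays.

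The cost is one sentence. The stratum is known from randomisation, and pain duration and recent care are already collected at baseline, so no new data are needed.
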